# Qualitative Process Evaluation

To explore both trial and intervention processes, following MRC guidance and using programme theory, we will qualitatively explore contextual factors, implementation processes, and intervention mechanisms of action to fully understand how nurse administered SRT is provided and received in oncology settings. This work complements the quantitative success criteria outlined in Table 1 above. Specifically, we will evaluate how intervention training is delivered to nurses and its acceptability to them, how the intervention is administered by nurses and whether intervention fidelity is maintained, the patient’s response to the intervention, how they interact with it, what they do as a result and any unexpected consequences. We will also explore any contextual factors within clinics and the wider health service environment that affect intervention implementation during the trial, increasing understanding of barriers and facilitators to intervention implementation, providing insights for a future trial and for potential future scale up. To explore these issues, in-depth semi-structured interviews / focus groups (telephone, online, face-to-face) will be conducted by the researcher across both study sites, and we will use theoretical frameworks designed explicitly to understand implementation processes. The sample size for this qualitative process evaluation is 20 [15 patients (10 from SRT arm, 5 from control arm) and 5 clinical staff (including the nurse therapist and those responsible for patient recruitment)].

# Data Analysis

As this is a pilot study, interpretation of the results will be considered with reference to the MRC Framework for Complex Interventions. As they relate to feasibility, no formal sample size calculation has been performed for our primary aim. Details of patient screening, recruitment, retention, withdrawal, adherence, acceptability and follow-up will be reported descriptively as outlined in table 1 above. Success criteria for these domains are summarised as follows: recruitment – 80% of target achieved; retention - <30% attrition; therapist adherence - >70% of SRT elements covered; patient engagement - attendance at 2/4 SRT sessions; control group contamination - <10% of SHE patients receive SRT; outcome measure completion - >70% of questionnaires fully completed.

To fulfil our secondary aim, between group comparisons of ISI 6-weeks post-randomisation will be done using t-tests or Mann-Whitney tests. Based on a mean difference in ISI of 4.2 between groups ([12](#_ENREF_12)) and an estimated standard deviation of 4.5 ([17](#_ENREF_17)) a sample size of 20 in each arm is required to achieve a power of 80% with a 5% significance level (we will aim to recruit 25 patients to each arm of the trial to accommodate our assumed dropout rate of 20%). The results from this feasibility RCT will help to refine the sample size calculation for a future definitive RCT.

# Public and Patient Involvement (PPI):

In preparation for commencement of this trial, we have recruited 5 members of our (previously established) PPI network to help shape the research questions, develop the project design, select suitable outcome measures, advise on the recruitment and data collection strategy, and contribute to proposal writing and editing. This ensures that patient wellbeing and improved patient care are central to our proposed methodology. Two PPI colleagues will be members of the study steering group, and one is a co-applicant on this project. Our PPI network also identified three key groups who will benefit most from the results of this project and will be key targets for our wider collaboration and communication strategy:

1. Patients – our results will inform the development of patient information resources, focusing on prioritising sleep health throughout cancer treatment. This will ensure that newly diagnosed breast cancer patients are informed about ways to minimise sleep disruption whilst undergoing cancer treatment and recovery. It will also open the door for patients to have sleep-focused conversations with clinicians, currently a neglected component of supportive cancer care.
2. Clinicians – our results will enable healthcare professionals who care for breast cancer patients to implement, alter, or augment sleep treatment protocols and signpost patients to relevant support services.
3. Charities – we work in partnership with numerous breast cancer charities, who will publicise our research outcomes on their websites and other patient communication resources. They will use our results to improve staff training programmes, ensuring they are more effectively able to support newly diagnosed patients with sleep difficulties.

# Adverse Event Ascertainment and Reporting

12.1 Definitions of Adverse Events, Serious Adverse Events, and Unanticipated Problems

Adverse events (AEs) will be defined as any unwanted medical event, reaction or side effect that occurs during the research study. Any relationship to study procedures will be determined and each AE defined as either unrelated or possibly, probably, or definitely related to participation in the study. The severity of the AEs will be determined by the type and outcome of the AE. Serious AEs (SAEs) are classified as such if the event results in death, disability, hospitalisation, deformation, congenital abnormality birth defects or any medical events that might lead to the outcomes listed above. The classification of the AE is determined irrespective of the relationship to the study interventions. An adverse event will be classified as an unanticipated problem (UP), if the AE is unexpected, if it is related or possibly related to the study procedures, and if the occurrence indicates that the participants or others are placed at greater risk by completing the study that previously assumed.

12.2 Unsolicited/Solicited Assessment and Reporting of Adverse Events and Unanticipated Problems:

AEs will be assessed systematically using a side effects inventory. Patients will also be encouraged to disclose any AEs, new symptoms or major life events during each assessment (unprompted side effects assessment). Additionally, sleep diaries and self-report questionnaires will be reviewed for any emerging symptoms. All AEs will be recorded in an adverse event reporting form, where a detailed description of the event and follow-up action will be recorded. Additionally, the form will provide an opportunity to record whether the event is classified as serious, whether it is related to the study procedures, and whether it is an unexpected AE (see definitions above). The adverse event form will be passed to the CI for review. All SAEs will be reported to the Ethics Committee within 48hrs and UPs that do not meet criteria for SAEs will be reported to the CI within 48hrs, who is responsible to reporting to the Ethics Committee within 30 days. All remaining AEs will be collated for the steering group committee.

# Data and Safety Monitoring:

An internal steering group committee, consisting of the study team, the patient advisory panel members and one external independent advisor ([name], University of Strathclyde) will review subject safety and data collection. The committee will have biannual meetings, where participant safety and data collection will be discussed. This includes AE reporting, withdrawals and dropouts from the study and progress with data collection.

# Criteria for Intervention Discontinuation

This study will be stopped prior to its completion if: (1) the intervention is associated with adverse effects that call into question the safety of the intervention (> 20% of participants develop a SAE related to the study); or (2) any new information becomes available during the trial that necessitates stopping the trial; or (3) other situations occur that might warrant stopping the trial. Given previous research on SRT in breast cancer, it would appear unlikely that these thresholds will be met in this study. Any decisions regarding discontinuation of the treatment would be discussed and made in consultation with NHS ethics and steering group committees.

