# Study Objectives:

1. To determine rates of participant recruitment and retention
2. To determine intervention fidelity
3. To determine outcome measure completion
4. To determine intervention acceptability

We wish to formally consider issues of recruitment and retention, fidelity, completion of outcome measures, and acceptability, to inform the future development of a definitive multi-centre RCT. Our success criteria for moving forward to full trial are based on a similar pilot RCT of breast cancer patients with insomnia ([16](#_ENREF_16)) and a RCT of Sleep Restriction Therapy in primary care ([17](#_ENREF_17)).

Table 1. Overview of objectives and success criteria

| **Objective** | **Quantitative success criteria** | **Quantitative measurement** | **Timepoint(s) of evaluation** | **Qualitative insights (evaluated throughout)** |
| --- | --- | --- | --- | --- |
| **Recruitment and retention rates** | Recruitment - 80% of target achieved | Enrolment logs for all consenting patients. Pre-screen failure logs for patients who meet inclusion criteria but are not enrolled | Screening | Understanding trial implementation and participation / offer of uptake |
|  | Retention -  <30% attrition rate | Completion of outcome measures | 12 weeks post randomisation |  |
| **Intervention fidelity** | Therapist adherence - >70% of SRT elements covered during sampled sessions | Independent clinician review of recorded SRT sessions and  completion of fidelity rating scale | 6 weeks post randomisation | Understanding therapist and patient perspectives on delivery and receipt of SRT sessions |
|  | Patient engagement -attendance at 2/4 SRT sessions | Intervention attendance logs | During intervention phase |  |
|  | Control group contamination - <10% of SHE patients receive SRT through nurse therapist | Client Service  Receipt Inventory | 6 weeks and 12 weeks post randomisation |  |
| **Outcome measure completion** | >70% of questionnaires fully completed | Completion of outcome measures | Baseline, 6 weeks and 12 weeks post randomisation | Explore the acceptability of the outcome measures for clinicians and patients |
| **Intervention acceptability** |  |  |  | Exploration of cancer journey, service ecology, role of early insomnia intervention and experiences of SRT or SHE. |

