# Study Design

A pilot, two-centre, two-arm, parallel group, block randomised (1:1) controlled trial will compare SRT with a SHE control. Both groups will continue to receive standard breast cancer treatment as usual (TAU). Consistent with the requirements of a pragmatic trial, there will be no limitations upon usual care for either group. In this way, the trial represents a comparison of SRT+SHE (+TAU) vs. SHE (+TAU), permitting clear judgements to be made regarding the relative clinical utility of SRT. Due to the nature of the SRT intervention, the therapist and patients cannot be blinded to treatment allocation. However, the statistician will be blinded to treatment allocation (i.e., SRT or SHE) until after analysis is complete.

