We aim to randomise 40 patients (n=20 in each trial arm), and conservatively estimate that we will recruit 5 patients per month across both sites in a 10-month recruitment window (assuming a dropout rate of 20%). This represents <10% of the total number of patients seen per month in these clinics. NHS Greater Glasgow and Clyde and NHS Grampian serve a combined population of around 1.7M. In the NHS GGC South Sector breast service, based at Gartnavel General Hospital, there are 550 new breast cancers each year, with over 60% of this population undergoing surgery as their primary treatment. In NHS Grampian, 545 new breast cancers (screening and symptomatic pathways) were diagnosed in 2021. About 84% of these newly diagnosed patients received surgery as their primary treatment. Of these, we conservatively estimate that 40% will meet criteria for acute insomnia (n=315). From these, we aim to randomise patients to take part in the study.

- 1. Study Assessment Points

After randomisation to SRT or SHE, patients will be sent an email with a link to complete a baseline (pre-intervention) assessment of sleep, fatigue, and mental health (questionnaires can be completed over the telephone or on paper should the participant prefer this). Patients will also be required to complete the consensus sleep diary and wear an actigraphy device for 7 days prior to commencement of SRT/SHE to record sleep and rest/activity rhythms. Within-treatment session outcomes for SRT will also be explored using sleep diaries and actigraphy. After completion of the baseline assessment, patients will either be referred to the nurse therapist for commencement of the SRT protocol or provided with the SHE resource. At 6 weeks, and 12 weeks post-randomisation, patients will be requested to complete the same battery of questionnaires as during the baseline assessment. Following completion of the final study assessment (12 weeks post-randomisation), those randomised to the SHE condition will be offered the opportunity to complete the SRT protocol without the requirement to complete any further assessments.

- 1. Primary and Secondary Outcomes

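### The only numeric safety stopping trigger is meant to judge SRT but names no arm; read literally it pools both arms, so up to 40% of SRT patients could have a related SAE with the trigger unmet

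*Protocol*

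**What the plan says.** The protocol section Criteria for Intervention Discontinuation lists three grounds for stopping early. The first applies if "the intervention is associated with adverse effects that call into question the safety of the intervention", and a bracket makes this concrete: "> 20% of participants develop a SAE related to the study". The other two, new information and other situations, carry no number. The section then remarks that earlier SRT research makes reaching the thresholds unlikely, so the intervention being judged is SRT. It ends: "Any decisions regarding discontinuation of the treatment would be discussed and made in consultation with NHS ethics and steering group committees".

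Other sections that bear on the denominator:

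- Study Design describes a "block randomised (1:1) controlled trial will compare SRT with a SHE control", and states that "the statistician will be blinded to treatment allocation" until the analysis is complete.
- Procedures (Randomisation) gives the size: "We aim to randomise 40 patients (n=20 in each trial arm"). Data Analysis gives 25 per arm to allow for 20% dropout.
- Interventions (Sleep Hygiene Education): control patients get a booklet and one call from the research assistant, and the SRT nurse therapist plays no part. Procedures (Study Assessment Points) offers them SRT only after the 12-week assessment.
- Adverse Event Ascertainment and Reporting grades relatedness as unrelated, possible, probable or definite, and the relation is to taking part in the study, not to the arm received. SAEs go to the Ethics Committee within 48 hours.
- Data and Safety Monitoring: the steering group meets twice a year.

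**The concern.** The purpose of the rule and its denominator do not match. The rule asks whether SRT is safe, but the number it watches is the proportion of all trial participants with a related SAE. In a 1:1 trial about half of those participants are not given SRT during the assessed period. If related SAEs arise mainly from SRT, the pooled proportion is roughly half the SRT proportion.

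The mismatch also works in the other direction. Because relatedness is to study participation and includes possible relation, a control patient can contribute an event that says nothing about SRT. The pooled proportion is therefore not an estimate of the SRT rate.

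At stake is whether the one numeric safety rule in the protocol would respond at the level it states. The protocol's Background says that there are no efficacy studies of SRT in breast cancer patients or in acute insomnia, and that tolerability still has to be evaluated. The rule matters most if the expectation of few harms proves wrong.

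**Working it through.** **Arm sizes.** The protocol gives no operating figure for the trigger, but the arm sizes can be checked. For an ISI difference of 4.2, SD 4.5, two-sided 5% (sidedness assumed) and 80% power, the t-test calculation gives 19.03 per arm, rounded up to 20. Then 20 / (1 − 0.20) = 25. Both stated sizes reproduce, and both are used below.

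**Literal rule.** Let n be the number per arm, x the SRT patients and k the control patients with a related SAE. The rule is unmet while (x + k) / 2n ≤ 0.20, that is, while x ≤ 0.40n − k.

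- n = 20: unmet at 8/40 = 20.0%, first met at 9/40 = 22.5%.
- n = 25: unmet at 10/50 = 20.0%, first met at 11/50 = 22.0%.

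Largest SRT count that leaves the literal rule unmet:

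| Control patients with a related SAE (k) | SRT, n = 20 | SRT, n = 25 |
|---|---|---|
| 0 | 8 (40%) | 10 (40%) |
| 1 | 7 (35%) | 9 (36%) |
| 2 | 6 (30%) | 8 (32%) |
| 3 | 5 (25%) | 7 (28%) |
| 4 | 4 (20%) | 6 (24%) |

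The dilution is not confined to full enrolment. With 10 per arm and k = 0, 4 of 10 SRT patients gives 4/20 = 20%, still unmet.

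**SRT denominator.** The rule is met once x > 0.20n: 5 of 20 (25%) or 6 of 25 (24%), whatever happens among controls. With k = 0 the literal rule needs 9 of 20 (45%) or 11 of 25 (44%).

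**Illustration with assumed rates.** The protocol gives no expected SAE rate, so the rates below are assumptions. Exact binomial, n = 20, one check at full enrolment. Literal rule with no control events: P(Bin(20, p) ≥ 9). SRT denominator: P(Bin(20, p) ≥ 5). The middle column adds Bin(20, 0.10) control events to the SRT count and takes the chance of 9 or more in total.

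| True SRT rate p | Literal rule, control rate 0 | Literal rule, control rate 10% | SRT denominator |
|---|---|---|---|
| 5% | <0.001 | 0.002 | 0.003 |
| 10% | <0.001 | 0.015 | 0.04 |
| 20% | 0.01 | 0.13 | 0.37 |
| 30% | 0.11 | 0.41 | 0.76 |

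At 5% neither version realistically fires. They separate mainly at SRT rates at or above the stated 20%.

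**The case against.** **The context allows an SRT-only reading.** The threshold sits in a bracket explaining the safety of the intervention, under a heading about discontinuing the intervention, and the next sentence is about SRT. On that reading the trigger is already 5 of 20 or 6 of 25. This stands as a possibility, and a reader should not infer that the sponsor intends a pooled count; the document does not show it. But the protocol does name an arm when it means one, as in the contamination criterion "<10% of SHE patients receive SRT through nurse therapist". As written, two teams could apply two different rules, one met at 5 SRT patients and one at 9.

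**40% is an extreme case.** It requires no related SAE among controls. This stands: 40% is the maximum, and the table shows how it falls.

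**Other safeguards exist.** SAEs reach the Ethics Committee within 48 hours without waiting for a steering group meeting, the non-numeric criteria allow stopping at any time, and discontinuation is decided in consultation with both committees. This stands and reduces the practical consequence considerably. A reader might infer that the trial would have to continue until 9 SRT patients were harmed. Nothing in the protocol obliges it to continue below the threshold.

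**The probabilities rest on assumed rates.** True, and the protocol considers reaching the thresholds unlikely. The counts do not depend on those rates.

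**Contamination.** The under-10% figure is a feasibility success criterion. It does not cap how many control patients might receive SRT, so it cannot be used to bound exposure. The argument needs only the 1:1 allocation and the deferral of SRT for controls until after week 12.

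**Conclusion.** The point holds as a defect in the wording of the one numeric stopping rule. Taken literally, the rule can stay unmet at an SRT related-SAE proportion of up to twice the stated 20%: 8 of 20 or 10 of 25 with no related SAE among controls, and fewer if controls have events. This rests on the literal reading of the denominator, equal arms, and controls not receiving SRT in the assessed period.

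It does not show that safety oversight is lacking, that the pooled count is intended, or that SRT is expected to be harmful. The prompt reporting and the discretionary criteria are real protection, but they leave the threshold itself unchanged. The change should be made because it is cheap and removes an ambiguity in a safety rule. It is not grounds for holding the trial.

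**What to change.** Reword criterion (1) so that it is met when more than 20% of those randomised to SRT have had at least one SAE judged possibly, probably or definitely related to the study. Report the corresponding control proportion to the steering group separately.

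Cost: a wording change and one tally by arm. No extra patient data are needed, since seriousness and relatedness are already recorded for each event. Someone other than the statistician should prepare the tally, so that the blinding set out in Study Design is kept.

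Downside: the trigger is reached at fewer events. At an assumed true SRT rate of 10%, a single check at 20 SRT patients meets it with probability 0.04. Repeated checking raises this: if the rule is checked after every SRT patient up to 20, each patient's status being known before the next is counted, the probability is 0.43, or 0.18 if checking starts only at the tenth.

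A minimum number and a checking schedule are for the sponsor and the committees, and are not part of this fix. A minimum of 10, for example, would leave the first nine SRT patients with no numeric trigger. While recruitment continues, some of those randomised to SRT will also still be in the baseline week (they "wear an actigraphy device for 7 days prior to commencement of SRT/SHE"). Whether to count only those who have started SRT is likewise a choice for the sponsor and the committees.
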